# Examining Different Motor Learning Paradigms for Improving Balance Recovery Abilities Among Older Adults, Random vs. Block Training—Study Protocol of a Randomized Non-inferiority Controlled Trial

**DOI:** 10.3389/fnhum.2021.624492

**Published:** 2021-02-25

**Keywords:** elderly people, postural balance, falls, balance perturbation training, random training, block training

## Abstract

**Introduction**: Falls are the leading cause of fatal and nonfatal injuries among older adults. Studies showed that older adults can reduce the risk of falls after participation in an unexpected perturbation-based balance training (PBBT), a relatively novel approach that challenged reactive balance control. This study aims to investigate the effect of the practice schedule (i.e., contextual interference) on reactive balance function and its transfer to proactive balance function (i.e., voluntary step execution test and Berg balance test). Our primary hypothesis is that improvements in reactive balance control following block PBBT will be not inferior to the improvements following random PBBT.

**Methods and Analysis**: This is a double-blind randomized controlled trial. Fifty community-dwelling older adults (over 70 years) will be recruited and randomly allocated to a random PBBT group (*n* = 25) or a block PBBT group (*n* = 25). The random PBBT group will receive eight training sessions over 4 weeks that include unexpected machine-induced perturbations of balance during hands-free treadmill walking. The block PBBT group will be trained by the same perturbation treadmill system, but only one direction will be trained in each training session, and the direction of the external perturbations will be announced. Both PBBT groups (random PBBT and block PBBT) will receive a similar perturbation intensity during training (which will be customized to participant’s abilities), the same training period, and the same concurrent cognitive tasks during training. The generalization and transfer of learning effects will be measured by assessing the reactive and proactive balance control during standing and walking before and after 1 month of PBBT, for example, step and multiple steps and fall thresholds, Berg balance test, and fear of falls. The dependent variable will be rank transformed prior to conducting the analysis of covariance (ANCOVA) to allow for nonparametric analysis.

**Discussion**: This research will explore which of the balance retraining paradigms is more effective to improve reactive balance and proactive balance control in older adults (random PBBT vs. block PBBT) over 1 month. The research will address key issues concerning balance retraining: older adults’ neuromotor capacities to optimize training responses and their applicability to real-life challenges.

**Clinical Trial Registration**: Helsinki research ethics approval has been received (Soroka Medical Center approval #0396-16-SOR; MOH_2018-07-22_003536; www.ClinicalTrials.gov, NCT04455607).

## Background

One out of four older adults will fall each year (Bergen et al., 2016), and the medical cost in 2015 for fatal and nonfatal fall-related injuries was 50 billion dollars (Centers for Disease Control and Prevention, 2017; Florence et al., 2018). The psychological impact of a fall often results in increasing self-restriction of activities and a decrease in quality of life (King and Tinetti, 1996; Rubenstein, 2006; Bergen et al., 2016).

Most fall prevention exercise programs incorporate balance practice which involves volitional movements (Gillespie et al., 2003, 2012; Lord et al., 2003; Wolf et al., 2003; Hue et al., 2004; Sihvonen et al., 2004; Skelton et al., 2005; Liu-Ambrose et al., 2008; Clemson et al., 2012). In a systematic review that included 81 trials (*n* = 19,684), Sherrington et al. (2019) found that training programs that included voluntary exercises (e.g., Otago program, FAME, and tai chi) reduce the rate of falls by 23% [relative risk (RR) 0.77; confidence interval (CI) 0.71, 0.83] and reduce the rate of fallers by 15% (RR 0.85; CI 0.81, 0.89). However, it is believed that balance recovery strategies that are evoked by an external unexpected loss of balance, i.e., unexpected perturbations, *cannot* be trained through voluntary exercises. In view of the evidence that the neural balance control differs in some fundamental ways in comparison to balance reactions that are evoked unexpectedly when balance is lost, it can be argued that training approaches for preventing falls should involve the use of unexpected perturbations during training (Maki et al., 2008). There is now accumulating evidence that shows the superiority of balance training that included unexpected perturbation exercises. Among older adults, just 24 perturbations within a single session of perturbation-based balance training (PBBT) is sufficient to lead to lasting improvements (i.e., 6–12 months) in reactive balance control (Bhatt et al., 2012) and prevent falls in daily life (Pai et al., 2014a). In a systematic review, it was found that older adults who participated in a PBBT that challenged the mechanisms responsible for dynamic stability could adapt in a reactive manner (Mansfield et al., 2015). Furthermore, they showed a reduction in the rate of falls by 46% and the diverse risks of falls (Mansfield et al., 2015).

Several studies have evaluated perturbation-based training during walking in older adults (Shimada et al., 2004; Mansfield et al., 2010; Halvarsson et al., 2011; Grabiner et al., 2012; Lurie et al., 2013; Pai et al., 2014a; Kurz et al., 2016; Okubo et al., 2017; McCrum et al., 2017). In another systematic review (Gerards et al., 2017), the authors reported that the PBBT that incorporates multiple perturbation types and directions might be of most benefit to improve balance. Studies reported that PBBT was accepted by older adults (Shimada et al., 2004; Mansfield et al., 2007; Melzer et al., 2007b; Pai and Bhatt, 2007; Lurie et al., 2013) and reported improvements in balance performance even after a single training session (Pai et al., 2014a). All the above training programs did not explore the skill acquisition of random practice compared to block practice in terms of the directions of perturbations of unexpected PBBT for older adults.

The process of skill acquisition relies on the interaction between cognition and motor control. One demonstration of this interaction has been termed the contextual interference (CI) effect (Lee and Magill, 1983). For example, practice schedule, the influence of the order in which training materials are presented to the learner, may influence learning abilities (Jamieson and Rogers, 2000). In training programs, the practice schedule is mainly divided into blocked or random practice. We define blocked practice as practicing a single task repeatedly before moving on to the next task (for example, train only unexpected loss of balance to the right direction, i.e., right balance reactive stepping, in a specific training session). Random practice is defined as practicing the tasks in a pseudo-random order (Shea and Morgan, 1979) such that each task is not practiced consecutively (for example, train balance recovery, including reactive stepping to the right/left/forward/backward randomly at the same training session). There is evidence that suggests that random training can improve motor learning [from pressing a button in response to a light cue, automated teller machine (ATM) operation, hand grasp as a response to a stimulus and knocking down six (changing) barriers, isometric pinch force to perturbation training, et cetera (Shea and Morgan, 1979; Del Rey, 1982; Kausler et al., 1990; Jamieson and Rogers, 2000; Guadagnoli and Lee, 2004; Bhatt and Pai, 2009; Mansfield et al., 2010; Hurt et al., 2011; Bhatt et al., 2012; Fazeli et al., 2017)]; on the other hand, others suggest that block training (cognitive memory task, balance perturbation training, seat to stand training, and isometric pinch force control) is more effective (Del Rey, 1982; Lazarus and Haynes, 1997; Pavol et al., 2002, 2004; Lin et al., 2008; Van Ooteghem et al., 2009; Pai et al., 2014a, b; Dijkstra et al., 2015; Coelho and Teixeira, 2017, 2018; Coelho et al., 2018). Additionally, a high CI effect (i.e., random practice) may create a poorer performance acquisition but enhance learning and better retention or transfer performance. Another research (Wright et al., 2016) has shown that in high CI, brain areas that are functionally significant for motor learning are recruited earlier. Lage et al. (2015) studied the correlation between different practice schedules and engagement of cortical brain areas. In their review that included 10 studies of different motor skill acquisitions, they found that there is greater activation of neural structures during random practice than during block practice. Additionally, random practice had a greater involvement of cognitive processes. On the other hand, de Xivry and Lefèvre (2015) found that different perturbation schedules did not lead to a more or less stabilized motor memory. A recent systematic review (Graser et al., 2019) of 25 studies examining the role of the practice order in children showed limited evidence for the benefit of blocked practice over random practice in regard to acquisition and retention; only for transfer there is moderate consistent evidence for the benefit of random practice over blocked practice. An additional approach of perturbation training is utilizing a split-belt training paradigm in which a person could walk on a treadmill with two belts moving at different speeds. Shimada et al. (2004) showed a significant improvement in balance function and a reduction in the number of falls (21% lower) in the split treadmill exercise. However, most falls are the result of unexpected perturbation, such as stumbling or slipping while walking, and not the result of walking on a different walking speed (Gabell et al., 1985).

Given the importance of balance recovery including reactive stepping in avoiding falls and the fact that balance loss is always unexpected and multidirectional, it is important to explore which PBBT program (random PBBT vs. block PBBT) is more effective or noninferior for balance recovery skill acquisition. To our knowledge, only a handful of studies (Pavol et al., 2002, 2004; Bhatt and Pai, 2009; Van Ooteghem et al., 2009; Hurt et al., 2011; Bhatt et al., 2012; Pai et al., 2014a, b; Dijkstra et al., 2015; Coelho and Teixeira, 2017, 2018; Coelho et al., 2018) published to date used some principles of motor learning theory to achieve the maximum skill acquisition, retention, and generalization of these learned skills. Unlike other forms of exercise, improved reactive balance control with PBBT seems to occur with few repetitions (McCrum et al., 2017) and is preserved for several months after training (McCrum et al., 2017).

From a fall-prevention standpoint, an important aim of a PBBT is that learned motor skills (i.e., reactive balance performance) create a fast learning process, which can be generalized to a wide variety of everyday situations (i.e., real-life situations), which may require rapid balance recovery maneuvers. In general, motor learning research suggests that conditions during training should be varied randomly to optimize motor learning [challenge point framework (CPF; Guadagnoli and Lee, 2004)]. This would mean delivering perturbations from various directions in a randomized fashion during PBBT and different phases of the gait cycle. To our knowledge, no study has investigated whether a constant or random practice is more effective for motor skill acquisition, retention, and transferring motor tasks when older adults are training to improve their ability to recover from an unexpected loss of balance during walking. Our proposed study will incorporate similar principles with the use of a mechatronic device that can perturb participants unexpectedly and in multidirectional ways during treadmill walking. It is not known whether random PBBT better improves balance reactions in terms of the period of PBBT than block PBBT. In this research, we will address a key question about the generalizability of balance intervention and the underlying locomotor plasticity in older adults using random vs. block PBBT. The primary aim of this study is to determine the effect of block PBBT on reactive balance control among older adults (i.e., multiple- and fall-step thresholds). Our primary hypothesis is that improvements in reactive balance control following block PBBT will be not inferior to the improvements following random PBBT. The secondary purpose of this study is to determine the effect of block PBBT and random PBBT on balance proactive balance control and fear of falls. We hypothesize that, proactive balance, i.e., anticipatory balance control [Berg Balance Scale (BBS)] and fear of fall (FES-I), will cause similar effects in block PBBT and random PBBT.

## Methods and Analysis

### Study Design and Setting

This is a double-blind randomized controlled trial (Figure 1, flowchart) that follows the recommendations of SPIRIT 2013 (see Supplementary Appendix 1 for the SPIRIT study checklist). Older adults are randomly assigned to one of two groups: (1) random PBBT; and (2) block PBBT. Both groups are trained twice a week for 4 weeks. Compensatory (reactive) and anticipatory (proactive) balance control during standing and walking, functional balance, and fear of falling will be measured pre-training and post-training. Fall monitoring will be performed 6 months after the posttest (Table 1). The PBBT will be provided inside participants’ community centers or in their protected housing. The study was approved by the Helsinki ethics committee at Soroka Medical Center, Beer-Sheva, Israel [Soroka Medical Center approval #0396-16-SOR; Israeli Ministry of Health (MOH)_#2018-07-22_003536; www.ClinicalTrials.gov, NCT04455607].

**Figure 1 F1:**
[figure not shown]
Study flowchart.

**Table 1 T1:** Flowchart—overview of outcome measurements and time of assessment.

	T_0_	T_1_	T_T_	T_2_	T_3_
Recruitment	+				
Interview (in/exclusion)	+				
Consent form (and medical waiver)		+			
Balance assessment (balance reactions while standing and walking; postural stability)		+		+	
Randomization		+			
Questionnaires (BBS; MMSE; FES-1)		+		+	
Training documentation (perturbation progression; participant comments; adverse events)			+		
Fall monitoring					+
Satisfaction questionnaire				+	

*T_0_, prior to study; T_1_, baseline (pre-intervention); T_T_, training time; T_2_, post-intervention test; T_3_, follow-up (6 months post-intervention). Abbreviations: BBS, Berg Balance Scale; MMSE, Mini-Mental Scale Examination; FES-1, fear of fall questionnaire*.

### Participants

A convenient sample of 50 community-dwelling older adults will be recruited from retirement villages for older adults *via* advertisements, personal contacts, and word of mouth. Participants will be included in the study if they are 70 years or older and independent in daily living activities and walking without assistive devices. After completing medical history, volunteers will be excluded if one met the exclusion criteria [suffering from ischemic heart disease which limits exercise; suffering from COPD and uncontrolled blood pressure; suffering from serious vision problems; having a score under 24 on the Mini-Mental State Examination (MMSE); being under a year after hip or knee replacement or broken extremities; and having any neurological diseases or stroke]. All subjects will provide a medical waiver signed by their primary care physician clearing them to participate in moderate physical exercise. All subjects will sign an informed consent statement. Participants will be informed that this is an intervention method of a technology that aimed to improve balance while treadmill walking and that based on the literature, we hypothesize that they will be most likely improving their function. They will also be informed that the training might be difficult at the beginning and thus muscle soreness will occur and that they are free to withdraw from the study at any time point, without consequence. They may also be withdrawn from the study due to changes in their health status that affect eligibility.

### Recruitment, Randomization, Blinding, and Treatment Allocation

Participants will be reimbursed with $25 for travel expenses (e.g., public transit, taxi, or parking) they incur to attend data collection appointments. Participants will be assigned using randomization to one of the two groups. The random allocation sequence will be computer generated (Random Allocation Software version 1.0). Blocked randomization will ensure equal numbers allocated to each group. Group allocation will be performed centrally by the principal investigator, who will not be involved in recruiting, scoring assessments, or administering the interventions (i.e., concealed allocation). Outcome measures will be obtained by a research assistant who will be blinded to group allocation. Participants are also blinded to group allocation since they will train on the same mechatronic device.

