### Informed Consent

In case an older adult is willing to participate in the study, a researcher (HN) will explain the study and will provide the participant with the study information sheet, information form for the general practitioner, and their permission to participate in the study and consent form. Participants will be informed that in this study there are two types of interventions that expose the participants to perturbations during treadmill walking (random PBBT vs. block PBBT); both are expected to improve balance function. To maintain the motivation of older adults to participate, they will be offered to participate in “other” exercise programs after the training period. They are also informed that the training might be difficult in the beginning and thus some muscle soreness will occur and that participants are free to withdraw from the study at any time point, without consequence. Participants may also be withdrawn from the study due to changes in their health status that affect eligibility. HN will answer the participant questions about the study. Participants may discuss the study with their family members, friends, or healthcare providers. The informed consent process will be documented by research personnel.

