### Interventions

Block PBBT will be trained using a foretold magnitude and unidirectional perturbations during treadmill walking. The random PBBT will be trained using a computer-generated random multidirectional unexpected perturbation during treadmill walking. Each group will receive eight training sessions, twice a week for 4 weeks (Figure 2, Table 3, details of the training programs). Each session will last 20–30 min and will include 2 min of warm-up walking at participants’ preferred speed without any perturbations and 14–20 min of 35 unexpected perturbations while walking (based on the group motor learning technique). In the random PBBT, the perturbations will be given randomly every 20–40 s, and the training will end with a 2-min cool-down comfortable walking. The participants in the block PBBT group will be aware of the direction of the perturbation, given visual cues, and in each training session, only one perturbation direction will be trained. The goal of both training protocols (random PBBT and block PBBT) is mainly directed towards a cognitive understanding of the training and an improvement of self-confidence for exercises on higher perturbation magnitudes. Some general effects on muscle power and speed development, coordination, and conditioning (i.e., endurance) are expected. Everyone should progress to a higher perturbation magnitude (Figure 2, Table 3, the training programs).

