### Limitations

There is a risk that both random PBBT and block PBBT methods introduced here might be difficult at the beginning of the training; thus, muscle soreness will occur. Also, there is a risk of balance loss and fall; however, we will use a harness system to ensure that a fall will not occur. Since PBBT is a challenging training approach, there is a risk that older adults will stop participating in the program (dropout). Because the outcome measures in this study are related to balance function and risk for falls, it is unlikely that our results will be definitive regarding the ability of these PBBTs to translate to a reduced number of falls and injurious falls among older adults. We will monitor real-life falls in a 1-year period post-intervention, using a diary and monthly telephone calls, but the sample size for such analysis will be too small. However, we assume that due to the low sample and relatively fit older adults, the improvement in balance function will not carry over to real-life falls. Our study will address relatively healthy independent older adults; therefore, the results could not be implemented on frail elderly or other populations. Also, since the number of participants is small, the study has a pilot character. Also, data analysis will address the following question: what is the optimal sample size for the primary outcome parameter, which will be used to estimate the sample size for the larger trial. Finally, although the assessor and the participants in this trial are blinded, the therapist delivering the intervention cannot be blinded to intervention allocation, which potentially introduces a source of bias.

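### The trial is labelled double-blind because both arms share a device, but the block arm knows the perturbation direction and consent names both interventions, so only assessor blinding is supported

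*Protocol article*

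**What the plan says.** Study Design and Setting states: "This is a double-blind randomized controlled trial". The Abstract uses the same label. The section on recruitment, randomization and blinding says who is meant. The assessor comes first: "Outcome measures will be obtained by a research assistant who will be blinded to group allocation". Participants follow: "Participants are also blinded to group allocation since they will train on the same mechatronic device". No other reason for participant blinding appears in the article. Limitations repeats the claim ("although the assessor and the participants in this trial are blinded") and names only the therapist as unblinded.

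Three other places describe what participants are told and what they experience:

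- **Informed Consent:** "Participants will be informed that in this study there are two types of interventions that expose the participants to perturbations during treadmill walking". The two types are named in the same sentence as random and block PBBT.
- **Interventions:** "The participants in the block PBBT group will be aware of the direction of the perturbation, given visual cues". The same paragraph restricts each block session to one direction. The Abstract agrees: "the direction of the external perturbations will be announced".
- **Specificity:** the random arm gets right, left, anterior and posterior translations by software. In the block arm the direction stays fixed within a session.

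**The concern.** A participant is blind to allocation only if the arms cannot be told apart from what that participant perceives and has been told. Here the schedule of directions is itself the intervention under comparison, and it is delivered openly to the person being trained. Sharing a treadmill hides nothing about the schedule.

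What is at stake is the protection that the trial may claim for outcomes that depend on the participant's expectations or choices. The short FES-I and the Late-Life Function and Disability Instrument are self-reported. The perturbation tests behind the primary thresholds stop when the participant falls into the harness, grasps the examiner's hand or asks to stop (Data Collection and Outcome Measures). The last two depend at least partly on the participant. A reader who takes the label at face value would discount expectation effects on all of these. Limitations reinforces that reading by listing only the therapist's awareness as a source of bias.

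**Working it through.** No arithmetic applies. The check sets the blinding statements against the consent and intervention text.

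1. **What the label means here.** The therapist is conceded to be unblinded, so the two blinded parties must be the assessor and the participant. If participant blinding fails, the double-blind label fails with it.

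2. **What participants know beforehand.** The Informed Consent section says that they hear of two intervention types, and it names them. It does not say how fully the schedules are explained, and the information sheet is not shown.

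3. **What participants perceive in training.**

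| Feature | Block arm | Random arm | Same for the participant? |
|---|---|---|---|
| Device | BaMPer treadmill | BaMPer treadmill | Yes |
| Timing of perturbations | Unexpected | Unexpected | Yes |
| Directions within a session | One | Four, in random order | No |
| Knowledge of direction | Announced or visually cued | None | No |
| Perturbations per session (Table 3) | 35 | 35 | Yes |

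The rows come from the Abstract, Interventions, Specificity, Overload and Progression, and Table 3. The arms match on device, timing and number. They differ on the two features that a participant can notice directly.

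4. **Whether the difference is hard to notice.** It is not subtle. A block participant has 35 perturbations in one known direction in a session; a random participant has 35 spread over four directions. Each arm has eight sessions, so each participant has 8 × 35 = 280 planned perturbations in which to notice the pattern. The names given at consent also describe the patterns.

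5. **A conflict in the text.** Table 3, its note, Specificity, and Overload and Progression all call the perturbations *unannounced* in both arms. The Abstract and Interventions say that the block arm is told or shown the direction. The two agree only if *unannounced* refers to timing, which Overload and Progression says is unexpected in both arms. Otherwise they contradict each other. Neither reading restores blinding: even with no cue, a direction that never changes within a session shows the schedule.

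6. **What survives.** Nothing in the article contradicts assessor blinding, so the supported description is assessor-blinded.

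**The case against.** The strongest reply has four parts.

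- **Awareness is an inference.** The consent text names two intervention types but does not show that the schedules are explained. A participant needs to know the contrast to name the arm. This stands as a limit. A reader might infer that all 50 participants can identify their arm from the first session, or that all were told both schedules in detail; the document does not establish either. It supports *probably*. That is still enough against a flat statement that participants are blinded, whose only stated reason is the shared device.
- **Effect on the primary outcomes.** A fall in the assessment is defined by load cells registering at least 30% of bodyweight in the harness, and step thresholds are verified by motion capture. This also stands: only tests ended by request or hand grasp are exposed to participant choice in this way, and no frequency is given for them. The self-reported scales are not primary outcomes.
- **Direction of bias.** Participants hear the same about both arms: "random PBBT vs. block PBBT); both are expected to improve balance function". Nothing in the document says that expectation would favour one of them. This stands too.
- **The assessor.** A reader might go on to infer that a participant's remark will unblind the assessor. That is conjecture. The unblinded therapist is already disclosed in Limitations.

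One defence fails. Participants may be unaware of the study hypothesis, but the article claims blinding to group allocation, which is a different thing. Nor is this a detail that a condensed article may leave out: the article makes a positive claim and gives a reason that does not support it.

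**Conclusion.** The point holds as a misstatement of blinding status. The double-blind label and the two statements that participants are blinded are not supported by the design as described; assessor-blinded is. The conclusion rests on two facts in the text: both interventions are named at consent, and the block arm's direction is known and constant within a session. It also rests on the inference that participants can probably connect the two.

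No size can be put on the consequence, and no direction either. The exposure is confined to the short FES-I, the Late-Life Function and Disability Instrument, and threshold tests ended by request or hand grasp. It would go too far to conclude that the primary comparison is biased or that the load-cell falls are compromised. The correction changes what the trial can claim, and no change to the design or the sample size follows from it.

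**What to change.** - Replace the double-blind label with assessor-blinded in the Abstract and in Study Design and Setting.
- Remove the statement that participants are blinded, and the same-device argument, from the section on recruitment, randomization and blinding. Remove the matching claim from Limitations, which does not use the term double-blind but does call participants blinded.
- Add participant awareness to Limitations, naming the short FES-I, the Late-Life Function and Disability Instrument, and threshold tests ended by request or hand grasp.
- Reconcile *unannounced* in Table 3, its note, Specificity, and Overload and Progression with the announced or cued direction in the Abstract and Interventions, stating for each arm what was withheld: timing, direction or both.
- Tabulate by arm the tests ended by request or hand grasp, separately from load-cell falls. This assumes that the reason for stopping was recorded.

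The cost is wording, one table and a design that looks less strong. Trial Status puts the end of baseline and post-training data collection at March 1, 2021, days after publication on February 25, 2021. The fix is therefore kept to description and reporting, which can still be changed.
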